#### Sensitivity analysis

Sensitivity Analysis is defined as “ a method to determine the robustness of an assessment by examining the extent to which results are affected by changes in methods, models, values of unmeasured variables or assumptions” with the aim of identifying “results that are most dependent on questionable or unsupported assumptions” [45]. It has also been defined as a series of analyses of a data set to assess whether altering any of the assumptions made leads to different final interpretation and conclusions” [46].

With increasing rates of non-participation in surveys and studies, the inherent uncertainty and potential for bias that accompanies non-response increases. Different adjustment methods have been proposed. The choice of an adjustment method depends on the assumptions that are considered plausible regarding the nature of the non-participation and the type of additional sources of data that are available.

In our study no information about the invited persons that refused to participate to the study is available. We assume that the non-participants are missing at random i.e. that the probability of being missing is not dependent on unobserved data, given the observed data.

However since the issue of a possible participation bias is so essential we decided to perform a sensitivity analysis to assess the robustness of our prevalence figures. The sensitivity analysis will be based on three different approaches: (1) a post-stratification strategy, (2) a reweighting procedure and (3) an extreme case scenario i.e. simulation of the impact on the overall prevalence starting from two hypotheses: 1. All of the non-responders are smokers 2. None of the non-responders are smokers. We will compare the results of these simulations with the original prevalence figures [47].

### Study II (case-control study)

#### Study population and sample size

One hundred patients with COPD and a smoking history of more than 10 pack-years (cases) and one hundred patients with the same smoking history without COPD (controls) will be invited in the second study in order to reach the needed sample size of 2 × 70 patients.

The inclusion criteria for the cases and the controls include the following: 1) a smoking history of more than 10 pack-years and 2) age between 35 and 70 years.

The cases and the controls will be matched based on the following criteria: age group, sex, smoking history, level of pollution in living area, body mass index, comorbidity (cardio-vascular diseases index, systemic disease, and tuberculosis in anamnesis), and use of medications that may influence the inflammatory status.

The cases will include 100 participants that meet the following criteria: 1) smokers aged 35–70 years with a smoking history of >10 pack-years; 2) completely irreversible AL based on the following criteria: FEV_1_/FVC < 0.7 according to the GOLD criteria (fixed threshold) or FEV_1_/FVC < LLN; 3) COPD of stage II-IV according to the GOLD criteria (post-bronchodilation FEV_1_ < 80 % of the predicted value) or the LLN criteria (FEV_1_ below the LLN); and 4) a confirmed diagnosis of COPD by a pulmonologist after a comprehensive clinical examination.

The controls will include 100 participants based on the following criteria: 1) smokers aged 35–70 years with a smoking history of >10 pack-years and without COPD according to the GOLD or LLN criteria, 2) without asthma (absence of symptoms), 3) no history of allergies, and 4) free from the use of bronchodilators.

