In order to estimate the sample size needed for the case-control study the following formula was used $$ n=\left(\frac{r+1}{r}\right)\frac{\sigma^2{\left({Z}_{\beta }+{\mathrm{Z}}_{\alpha /2}\right)}^2}{{\left(d\mathrm{ifference}\right)}^2} $$ ; r stands for the ratio cases/controls (we choose for an equal number of cases and controls), *Z*_*β*_ = the desired power (for 80 % power *Z*_*β*_ = .84) , Z_*α*/2_ = the desired level of significance (for 0.05 significance level, Z_*α*/2_ =1.96), *σ*^2^ = the variance of the outcome variable (for Log hCRP = 0.25 ) and *d =* the difference in means that is considered meaningful (for log hCRP we used 0.4 as the minimum meaningful difference). The number of cases and controls needed was estimated in this way as 63. Taking into account a potential drop out of 10 % it was decided to involve 70 heavy smokers with established airflow limitation and 70 heavy smokers with normal lung function.

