## Results

Participants aged 35-70 years from the patient list from each center were selected using a random number generator; initially, 4419 individuals were invited to participate in the study. In total, 3133 individuals agreed to participate and met the inclusion criteria. In addition, 2974 participants demonstrated satisfactory quality on spirometry (after comprehensive quality assessment for reproducibility and acceptability) (Fig. 2). Basic spirometry analysis revealed 247 participants with obstructions before bronchodilation (FEV_1_/FVC < 0.7). Good-quality bronchodilator tests were obtained from 2388 participants. Of these participants, 162 were patients with AL (FEV_1_/FVC < 0.7), including 130 patients with irreversible lung obstruction (FEV_1_ < 200 ml or 12 % after bronchodilation).

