#### Why do some smokers develop COPD whereas others do not, and vice-versa for non-smokers?

Although cigarette smoke is widely acknowledged as the single most important risk factor for COPD, it is currently recognized that never-smokers may account for between one-fourth and one-third of all COPD cases [76]. The BOLD study reports three primary findings concerning this issue: 1) never-smokers are a substantial proportion (28 % of irreversible airway obstruction cases occur in never-smokers aged 40 to 98 years) of individuals with COPD, and they are typically not diagnosed with this disease; 2) more than two-thirds of never-smokers with moderate to severe airway obstruction are women; and 3) predictors of COPD in never-smokers include age, education, exposure to occupational hazards, childhood respiratory diseases, and BMI alterations.

In the ECLIPSE [25] study, Agustí et al revealed a distinct systemic inflammatory network pattern (inflammome) in patients with COPD that differs from that of smokers displaying normal lung function and that of non-smokers. However, systemic inflammation is not consistently detected in all COPD patients given that 30 % do not abnormally express any inflammatory biomarkers. The ECLIPSE study also revealed a subgroup of COPD patients displaying persistently elevated inflammatory biomarker expression who exhibit relatively similar lung function impairment and significantly increased all-cause mortality and exacerbation frequency. These inflamed patients may represent a novel distinct phenotype of COPD.

Increased levels of various biomarkers (WBCs, IL-8 and TNFα) were identified in smokers exhibiting normal spirometry results compared with nonsmokers, whereas similar levels of other biomarkers (CRP, IL-6 and fibrinogen) were detected between both groups [25].

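### The case-control target (63 needed, 70 enrolled, 100 invited) does not follow from its printed inputs, and the screening counts do not show that enough eligible cases exist

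*Protocol article*

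**What the plan says.** The case-control calculation stands under Study I, Sample size calculations. It compares two means with equal groups, 80 % power (Z = 0.84) and two-sided 5 % significance (Z = 1.96). The variance of log hCRP is 0.25 and the minimum meaningful difference 0.4. The stated result is 63 per group; after a 10 % dropout allowance, "it was decided to involve 70 heavy smokers with established airflow limitation and 70 heavy smokers with normal lung function".

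Study II, Study population and sample size, plans to invite 100 cases and 100 controls "in order to reach the needed sample size of 2 × 70 patients". Further down, the same section says: "The cases will include 100 participants that meet the following criteria". Those criteria are:
- age 35–70 and more than 10 pack-years;
- completely irreversible airflow limitation by the fixed ratio or the LLN;
- stage II–IV disease, or FEV1 below the LLN;
- a COPD diagnosis confirmed by a pulmonologist.

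Cases and controls are then matched on several factors, including age group, sex, smoking history, BMI, comorbidity and medication.

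Results gives the screening yield: 2974 acceptable spirometries, 2388 good-quality bronchodilator tests and, among those, 162 participants with FEV1/FVC below 0.7, "including 130 patients with irreversible lung obstruction". Table 1 reports smoking for the whole sample only: 917 current and 572 former smokers among 3114, or 47.8 %.

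**The concern.** Study II carries objective 4, the comparison of biomarkers and pneumoproteins between smokers with and without COPD. Its case number looks insecure in two ways.

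First, supply. Inviting 100 cases from a screened group with 130 irreversible obstructions leaves little room for the smoking, severity and diagnosis criteria. The Discussion itself cites evidence that "never-smokers may account for between one-fourth and one-third of all COPD cases".

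Second, the target appears not to match its own formula. If so, nobody can say whether a shortfall against 70 would matter, because the effect size the study is meant to detect is not settled. That effect size decides whether a smaller case series still answers objective 4.

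**Working it through.** **1. Reproducing the stated size.** The formula is n = ((r+1)/r) × σ² × (0.84 + 1.96)² / d², with r = 1, σ² = 0.25 and d = 0.4:

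2 × 0.25 × 7.84 / 0.16 = 24.5, so 25 per group; 25/0.9 = 27.8, so 28 with dropout.

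The stated 63 is not reproduced. Other readings do not give it either: one-sided testing gives 20, 90 % power gives 33, and treating 0.25 as the SD gives 7. Solving backwards:
- at variance 0.25, a difference of 0.25 gives 2 × 0.25 × 7.84 / 0.0625 = 62.7, so 63;
- at difference 0.4, the variance would have to be 63 × 0.16 / (2 × 7.84) = 0.64.

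Both amount to 0.5 SD, whereas the printed inputs amount to 0.4/0.5 = 0.8 SD. The dropout step does reproduce: 63/0.9 = 70.

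**2. What each reading implies.** Power = Φ(δ√(n/2) − 1.96), with δ in SD units. Detectable difference at 80 % power and variance 0.25 = √(3.92/n).

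| Evaluable per group | Power at 0.8 SD | Power at 0.5 SD | Detectable difference |
|---|---|---|---|
| 25 | 81 % | 42 % | 0.40 |
| 40 | 95 % | 61 % | 0.31 |
| 50 | 98 % | 71 % | 0.28 |
| 63 | 99 % | 80 % | 0.25 |

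**3. Supply of cases.** Start from 130. The share that must meet every remaining criterion is:
- for 100 invited: 100/130 = 76.9 %;
- for 70, if all who are eligible take part: 70/130 = 53.8 %.

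Only 2388 of the 2974 acceptable spirometries had a good-quality bronchodilator test, so 586 people are unclassified. Assuming the same yield among them, 130 × 2974/2388 = 162, and 100 invited needs 100/162 = 62 %.

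The pass rate is not reported. Smoking alone can be bracketed by assumption. The ever-smoker share among the 130 is unknown; the whole-sample share gives 130 × 0.478 = 62, and the cited literature (one-third to one-quarter never-smokers) gives 130 × 0.667 = 87 to 130 × 0.75 = 97.5. On the scaled count of 162, a share of 72 % (the article also cites 28 % never-smokers among irreversible obstruction) gives about 117. The pack-year, stage and diagnosis criteria then reduce any of these further, by amounts the article does not give.

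**4. Uptake.** Inviting 100 to obtain 70 implies 70 %. Screening achieved 3133/4419 = 71 %, so that assumption is in line with experience, and the number that must exist is 100 rather than 70. If the printed inputs are the intended ones, 28 enrolled at 70 % uptake needs 28/0.7 = 40 invited, or 40/130 = 31 % of the 130.

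**The case against.** A reader might infer that the target cannot be delivered because the study's own figures leave fewer than 100 smokers. The documents do not support that. Smoking status among the 130 is not reported, and the never-smoker fractions come from outside studies; one of them covers ages 40–98 rather than 35–70. A share only slightly above 75 %, namely 76.9 %, would reach 100 ever-smokers.

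Nor is 130 a ceiling. It counts fixed-ratio obstruction only, while Study II also accepts the LLN, and 586 people lack a usable bronchodilator test. The cohort takes in people obstructed before or after bronchodilation and repeats their spirometry. No text shown confines cases to this sample, the design and flow figures are not shown, and a condensed article may leave the recruitment source to the full protocol. All of this stands.

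Some of it cuts the other way. Results defines irreversibility with 200 ml or 12 %, Study III joins the two with and, and Study II asks for complete irreversibility; a stricter reading would shrink the pool. LLN-only cases may add little, since Background says the LLN may fall below 0.7 after about age 45 and only 19.8 % of the sample is 35–44.

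A reader might also infer that objective 4 is under-powered as stated. That fails: at the printed 0.8 SD, 26 pairs give Φ(0.8√13 − 1.96) = 82 %. The 0.5 SD effect appears nowhere in the article; it is only what 63 implies.

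Finally, the 1489 ever-smokers in Table 1 are not the number of available controls. They include people with obstruction, with 10 pack-years or fewer, or with the asthma, allergy or bronchodilator use that excludes controls.

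**Conclusion.** The point holds in a limited form. Two parts are firm: 63 does not follow from variance 0.25 and difference 0.4, which give 25, and 100 is used in one section both as the number invited and as the number included. The supply part is a well-founded doubt. About 77 % of the 130 would have to meet every further criterion, or 62 % of 162 if unclassified participants yield cases at the same rate, against 47.8 % ever-smokers in the sample as a whole. Obstructed participants probably smoke more than the whole sample, so the last figure is context, not an estimate.

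Whether a shortfall matters depends on the unsettled effect size. At 0.8 SD a much smaller series suffices; at 0.5 SD, 50 pairs give 71 % and 40 give 61 %. Either way the 63/70/100 figures need restating. This should be corrected before Study II recruits, but it does not invalidate the design.

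**What to change.** 1. Query the central database for participants with irreversible limitation (fixed ratio or LLN), more than 10 pack-years, stage II–IV or FEV1 below the LLN, and a confirmed diagnosis. Report the count, and apply one definition of irreversibility throughout.
2. State whether cases come only from the RESPECT sample and, if not, from where else.
3. Correct either the printed variance and difference or the 63/70/100, and say which effect is considered meaningful.
4. Restate power, or the detectable difference, from the eligible count and a realistic uptake.
5. Use 100 only as the number invited.

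If the target rests on 0.5 SD and the count falls short, the ratio r already in the formula could be raised. Read as controls per case, it gives ((r+1)/r) × 7.84/0.25: 62.7 cases at 1:1, about 47 at 1:2 and about 42 at 1:3. The price is additional control assays and harder matching, and the number of eligible controls would need its own count.

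Items 1 to 5 cost one query and a few revised sentences. The article describes Study II as still to come, so they can be made before recruitment.

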The aim of our study is to gain a better understanding of the prevalence, pathogenesis and symptoms of early COPD. This study seeks to address the following specific objectives/research questions: 1) to estimate the prevalence of AL and COPD in adults 35-70 years of age in St. Petersburg and Arkhangelsk based on sex, age, environmental conditions, socioeconomic status and smoking status; 2) to compare the prevalence of COPD in the study population based on the GOLD and LLN criteria; 3) to identify the diagnostic value of various signs, symptoms and background characteristics for the diagnosis of COPD; 4) to determine whether differences in background characteristics, inflammatory biomarkers and pneumoproteins are evident between smokers with and without COPD; and 5) to describe co-morbidity, functionality and global health status in a cohort of newly diagnosed COPD patients.

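### Study II bars allergy history and bronchodilator use in controls only, so marker differences may partly reflect selection; nor can it estimate differences in the factors it matches on

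*Protocol article*

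**What the plan says.** All places are in the protocol article. Under Study II, Study population and sample size, two criteria apply to cases and controls alike: "1) a smoking history of more than 10 pack-years and 2) age between 35 and 70 years".

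Controls must further be free of COPD and "2) without asthma (absence of symptoms), 3) no history of allergies, and 4) free from the use of bronchodilators".

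Cases must meet spirometric and severity limits, show "completely irreversible AL based on the following criteria", and have "a confirmed diagnosis of COPD by a pulmonologist after a comprehensive clinical examination". No case criterion concerns allergy history or bronchodilator use.

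The groups are matched on "age group, sex, smoking history, level of pollution in living area, body mass index", on three named comorbidity items, and on "use of medications that may influence the inflammatory status". Allergy and asthma are not named as matching factors.

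Objective 4, at the end of the Background, is "to determine whether differences in background characteristics, inflammatory biomarkers and pneumoproteins are evident between smokers with and without COPD".

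The Study II laboratory section lists the markers to be compared. They include IL-4, IL-8, hs-CRP and TNFα in blood, and eosinophils in induced sputum from 30 cases and 30 controls.

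**The concern.** A case-control contrast can be read as a COPD contrast only if the groups are not also made to differ on something else that moves the outcome. Here the control group is cleared of allergy history and bronchodilator use and the case group is not. Some of the markers plausibly respond to allergy or to treatment. A difference could then appear with no COPD effect, or a real one could be enlarged or masked, depending on the direction of the shift.

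The second issue is what Objective 4 can get out of Study II. Matching makes the groups alike on the matched factors, so the matched sample carries no usable information on whether smokers with and without COPD differ in them. The section on questionnaires gives sex and age as examples of background characteristics, and both are matched.

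**Working it through.** **Eligibility, side by side**

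| Attribute | Controls | Cases |
|---|---|---|
| Allergy history | excluded | no criterion |
| Bronchodilator use | excluded | no criterion |
| Asthma | excluded, by absence of symptoms | no direct criterion; indirect screen by irreversibility and pulmonologist confirmation |

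The first two rows are one-sided. The third is only partly so.

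**Can modelling repair it?** The Statistical analysis section offers general multivariate correction. Let D be case status and A the presence of allergy history or bronchodilator use. Three of the four D-by-A cells can occur: cases with A, cases without A, and controls without A. The COPD contrast among people with A cannot be estimated, because no control is there. If a term for A is added to the model, the coefficient for D rests on cases without A against controls. That is the restricted comparison under another name. For cases with A, the COPD effect and the effect of A are not separable without extrapolation.

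**The plan's own sample-size figure.** The article prints 63 per group. Its formula with its stated inputs gives 2 × 0.25 × (0.84 + 1.96)² / 0.4² = 2 × 0.25 × 7.84 / 0.16 = 24.5, that is 25, so 63 is not reproduced. A difference of 0.25 with SD 0.5 would give it: 2 × 0.25 × 7.84 / 0.0625 = 62.7. The step 63 / 0.9 = 70 does reproduce. This is a separate matter. The illustration below uses the planned 70 per group and SD = √0.25 = 0.5 on log hs-CRP.

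**Size of a possible spurious difference.** Let q be the share of cases with A, and s the shift that A causes in log hs-CRP. Both are assumptions. The only related figure is self-reported asthma in Table 1, 179 of 3059 (5.9 %), which describes the whole sample and not the cases. With no true COPD effect and the SD held at 0.5:

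- bias b = q × s
- standard error = 0.5 × √(2/70) = 0.0845
- rejection rate = Φ(b/0.0845 − 1.96) + Φ(−b/0.0845 − 1.96)

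| q | s | b | b as share of 0.4 | rejection rate |
|---|---|---|---|---|
| 0.1 | 0.1 | 0.01 | 2.5 % | 5.2 % |
| 0.3 | 0.3 | 0.09 | 22.5 % | 18.7 % |
| 0.5 | 0.5 | 0.25 | 62.5 % | 84.1 % |

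The range runs from trivial to severe.

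**Medication matching.** If bronchodilators belong to the matched medications, a case who uses one needs a control who also does, and no such control is eligible. If they do not belong, use is unrestricted in cases and absent in controls. The text does not say which applies.

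**Background factors.** Matched: age group, sex, smoking history, pollution, BMI, cardiovascular index, systemic disease, tuberculosis history, and medication. Collected but not matched: socioeconomic status, occupational exposure, passive smoking, biomass fuel, and family history.

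**The case against.** A reader might infer that only controls are screened for asthma. The documents do not support that. Irreversible limitation and a pulmonologist's confirmation screen cases indirectly, and a questionnaire separates asthma from COPD before spirometry. These steps do not remove allergy history, bronchodilator use or every coexisting asthma. The Study III co-morbidity list in fact records asthma and allergic disease in patients with airflow limitation.

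A reader might infer that the biomarker contrast is confounded. What the documents support is that it may be. The share and the shift are not given, and medication matching may reduce the problem if it covers bronchodilators.

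A reader might infer that the background half of Objective 4 is void. That holds only for the matched factors. The unmatched ones listed above remain comparable within Study II. Objective 1 and the planned analysis of correlates of COPD already cover part of the rest, and Objective 4 is not expressly confined to Study II.

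A reader might also call the matching infeasible or excessive. The article gives no category counts and does not say whether matching is individual or by frequency, so feasibility cannot be judged. Matching on BMI is defensible for the biomarker comparison, since the Background names BMI as a determinant of systemic inflammation. BMI, comorbidity and medication could be consequences of COPD, but adjusting for them instead would remove the same component. The choice between matching and adjustment is a preference.

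Finally, some difference in airway symptoms is inherent in comparing diseased with undiseased smokers. That argument stands for symptoms. It does not explain a one-sided rule on allergy history.

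**Conclusion.** The point holds in a limited form. Allergy history and bronchodilator use are excluded from controls and unrestricted in cases, so a difference in allergy- or treatment-sensitive markers may partly reflect selection. Direction and size are unknown; the 5.2 % to 84.1 % range depends wholly on the assumed q and s. General covariate adjustment does not resolve it for cases with these attributes. Study II also cannot answer Objective 4 for its matching factors, but it can for the unmatched ones. The change is worth making now, because recruitment to Study II is described as still to come.

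**What to change.** 1. Make the allergy-history rule the same in both groups, preferably by dropping it for controls and adjusting for allergic disease, which the comorbidity questionnaire already records. Cost: some added variance. This leaves the bronchodilator rule one-sided, so a comparison restricted to bronchodilator-free cases would still be needed.

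2. Alternatively, keep the criteria and prespecify an analysis restricted to cases with neither attribute. Cost: fewer cases. With q from 0.1 to 0.5, 70 cases fall to between 63 and 35. With 70 controls kept and SD 0.5, power goes from 99.6 % to 97.2 % for a difference of 0.4, and from 82.1 % to 67.6 % for 0.25.

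3. Excluding such cases at entry is the costlier route. To keep 70 cases at the planned yield of 70 per 100 invited, 100/(1 − q) must be invited: 112, 125, 143, 167 or 200 for q = 0.1 to 0.5. The Results report 130 participants with irreversible obstruction by the fixed ratio, before the smoking and severity criteria.

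4. Do not carry the absence-of-symptoms item over to cases. It would remove symptomatic COPD, which the study means to describe.

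5. Reconcile the bronchodilator exclusion in controls with the medication matching, by stating whether bronchodilators count among the matched medications.

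6. State that differences in the matched factors will be examined in the unmatched smokers above 10 pack-years in Study I, where the factor is recorded. BMI needs checking, because the article lists it for the cohort but not among the Study I questionnaires. Keep the unmatched background factors in Study II. Cost: wording and one further analysis of existing data.
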